## Abstract

**Background:**

Multiple sclerosis (MS) is an autoimmune inflammatory disease of the central nervous system that causes myelin sheath damage and axonal degeneration. The glycolipid (2S, 3*S*, 4*R*)-1-O-(α-d-galactosyl)-2-tetracosanoylamino-1,3,4-nonaetriol (OCH-NCNP1 or OCH) exerts an immunoregulatory action that suppresses T helper (Th)1 cell–mediated immune responses through natural killer T cell activation, selective interleukin-4 production, and Th2 bias induction in human CD4-positive natural killer T cells.

**Objective:**

This trial aims to investigate the efficacy and safety of the immunomodulator OCH in patients with relapsing MS through 24-week repeated administration.

**Methods:**

This protocol describes a double-blind, multicenter, placebo-controlled, randomized phase II clinical trial that was initiated in September 2019. The participants were randomly assigned to either a placebo control group or an OCH-NCNP1 group and the investigational drug (3.0 mg) was orally administered once weekly for the 24-week duration. Major inclusion criteria are as follows: patients had been diagnosed with relapsing MS (relapsing-remitting and/or secondary progressive MS) based on the revised McDonald criteria or were diagnosed with MS by an attending physician as noted in their medical records; patients with at least two medically confirmed clinical exacerbations within 24 months prior to consent or one exacerbation within 12 months prior to consent; patients with at least one lesion suspected to be MS on screening magnetic resonance imaging (MRI); and patients with 7 points or less in the Expanded Disability Status Scale during screening. Major exclusion criteria are as follows: diagnosis of neuromyelitis optica and one of optic neuritis, acute myelitis, and satisfying at least two of the following three items: (1) spinal cord MRI lesion extending across at least three vertebral bodies, (2) no brain MRI lesions during onset (at least four cerebral white matter lesions or three lesions, one of which is around the lateral ventricle), and (3) neuromyelitis optica–immunoglobulin G or antiaquaporin-4 antibody-positive. Outcome measures include the primary outcome of MRI changes (the percentage of subjects with new or newly expanded lesions at 24 weeks on T2-weighted MRI) and the secondary outcomes annual relapse rate (number of recurrences per year), relapse-free period (time to recurrence), sustained reduction in disability (SRD) occurrence rate, period until SRD (time to SRD occurrence), no evidence of disease activity, and exploratory biomarkers from phase I trials (such as gene expression, cell frequency, and intestinal and oral microbiome).

**Results:**

We plan to enroll 30 patients in the full analysis set. Enrollment was closed in June 2021 and the study analysis was completed in March 2023.

**Conclusions:**

This randomized controlled trial will determine whether OCH-NCNP1 is effective and safe in patients with MS as well as provide evidence for the potential of OCH-NCNP1 as a therapeutic agent for MS.

**Trial Registration:**

ClinicalTrials.gov NCT04211740; https://clinicaltrials.gov/study/NCT04211740

**International Registered Report Identifier (IRRID):**

DERR1-10.2196/46709

## Introduction

Multiple sclerosis (MS) is considered to be an autoimmune disease triggered by environmental factors that act on a genetically susceptible host. Both major histocompatibility complex (MHC) and non-MHC genes are risk factors for the development of MS. In addition, environmental factors such as low vitamin D, low ultraviolet radiation exposure, cigarette smoking, obesity, and Epstein-Barr virus exposure can increase the risk for both the development of MS and a more severe disease course. Accumulating evidence suggests that dysregulation of the intestinal microbiome (dysbiosis) constitutes an important factor contributing to MS pathogenesis. The microbiome regulates T cell function, with both regulatory and pathogenic effects, thereby playing an important role in autoimmune responses [1].

MS is a cell-mediated autoimmune disease directed against central nervous system (CNS) myelin antigens involving both CD4+ and CD8+ T cells, especially the so-called pathogenic T helper (Th)17- and Th1-type and CD8 myelin autoreactive T cells. The development of MS is likely triggered or promoted by breakdown of the delicate balance between autoreactive T cells and regulatory lymphocytes [1].

Although MS has historically been considered a demyelinating disease of the CNS and white matter, in recent years, neurodegeneration of the cortical and deep gray matter has been recognized to play a role in the pathogenesis of MS. Cortical atrophy is associated with disease progression, which has emerged as one of the best predictors of neurological disability in MS [1].

According to a recent worldwide epidemiological study, the number of patients with MS is estimated to be 2.8 million, which has been increasing in every world region since 2013 [2]. The estimated total economic burden of MS in the United States is US $85.4 billion, with a direct medical cost of US $63.3 billion and indirect and nonmedical costs of US $22.1 billion [3].

Relapsing-remitting MS (RRMS) initially involves clinical relapses with near or complete recovery; however, recovery over time may be incomplete and disability often worsens [4]. Approximately 20% of patients with RRMS develop a progressive form of MS accompanied by chronic neuroinflammation. Such cases are referred to as secondary progressive MS (SPMS). The term “relapsing MS” (RMS) is used to describe the condition of patients with repeated relapses of either RRMS or SPMS.

As understanding of the pathomechanism of MS progresses, various disease-modifying drugs have been used in clinical practice, including sphingosine-1-phosphate receptor modulators (fingolimod, siponimod), a monoclonal antibody that selectively binds the α4 integrin subunit (natalizumab), and CD20 monoclonal antibodies (ofatumumab, ocrelizumab), resulting in an overall improvement of patient prognosis. However, there are patients for whom current treatments are ineffective and there are cases where current treatments are intolerable due to side effects. Furthermore, progressive MS remains refractory to current drugs and constitutes an unmet medical need [4]. These observations highlight the need for new, safer therapeutic oral agents.

In 1997, Kawano et al [5] reported the discovery of sponge-derived α-galactosylceramide (α-GC) as a glycolipid ligand that stimulates natural killer T (NKT) cells. However, because this glycolipid stimulates NKT cells and induces the production of both interleukin (IL)-4 and interferon (IFN)-γ, a search for glycolipids that selectively induce IL-4 production was initiated to treat Th1 cytokine–dependent autoimmune diseases such as MS. These efforts led to the discovery of (2S, 3*S*, 4*R*)-1-O-(α-d-galactosyl)-2-tetracosanoylamino-1,3,4-nonaetriol (OCH-NCNP1; hereafter referred to as OCH), which was detected during screening for glycolipids that selectively induce the production of Th2 cytokines [6].

OCH is a derivative (synthetic glycolipid) of α-GC with a shortened fatty-acid chain (sphingosine chain). The compound is a white to slightly yellow powder that is extremely insoluble in methanol or ethanol and is practically insoluble in water. OCH exhibits an immunoregulatory action that suppresses Th1 cell–mediated immune responses through NKT cell activation, selective IL-4 production, and Th2 bias induction in human CD4+ NKT cells [7].

Although the mechanism by which OCH induces Th2 bias in NKT cells is not fully understood, it has been suggested to involve both cell intrinsic and extrinsic factors [8,9]. As a cell intrinsic mechanism, IFN-γ production by NKT cells was reported to be more susceptible to the sphingosine length of the glycolipid ligand compared to IL-4 production, and the length of the sphingosine chain determined the half-life of NKT cell stimulation by CD1d-associated glycolipids. As an extrinsic regulatory mechanism, OCH suppresses the production of IFN-γ, not only by NKT cells but also by NK cells, compared with that of α-GC. OCH induced lower IL-12 production due to ineffective primary IFN-γ and CD40 ligand expression by NKT cells, which resulted in lower secondary IFN-γ induction.

Animal studies verified that OCH can be administered orally to control Th1 cell–mediated autoimmune pathology in mice, with efficacy against autoimmune disease models such as experimental autoimmune encephalomyelitis, collagen-induced myelitis [10], nonobese diabetes [11], and inflammatory enteritis [12].

We here describe a protocol for a feasibility study that will be conducted in patients with RMS to investigate the efficacy and safety of OCH immunomodulators. Through 24 weeks of weekly administration, this trial was performed to confirm changes in exploratory T cell and NK cell biomarkers that fluctuated in the phase I trial [13], as well as measures of efficacy, including recurrence, dysfunction, and magnetic resonance imaging (MRI) changes, and their association with combined endpoints. In alignment with past clinical trials [14,15] and European Medical Agency guidelines, the primary outcome will be the percentage of subjects with new or newly expanded lesions at 24 weeks on T2-weighted MRIs.

## Methods

### Study Design

This is a double-blind, multicenter, placebo-controlled, randomized phase II clinical trial with a 24-week duration. This trial investigates the efficacy and safety of the immunomodulator OCH in patients with RMS through 24-week repeated administration. The protocol was also designed to confirm exploratory biomarkers of T cells and NK cells that fluctuated in the phase I trial [13], as well as efficacy-related clinical endpoints, including relapses, disability, and MRI changes, and their association with combined endpoints. Recruitment opened in September 2019 and concluded in June 2021, with participants randomly assigned to either a placebo control group or an OCH group using a clinical-based management system (Translational Research Center for Medical Innovation, Kobe, Japan). The researchers were blinded to the participant group assignments, and the packaging appearance of the control and investigational drugs was confirmed to be indistinguishable.

An independent data monitoring committee will regularly audit all available data, including safety, and recommend trial continuation to the principal investigator.

### Selection Criteria

Inclusion and exclusion criteria for this study are provided in Textbox 1.

Inclusion and exclusion criteria.Inclusion criteriaPatients who provided written consent for trial participationPatients had been diagnosed with relapsed multiple sclerosis (MS), including relapse-remitting MS and/or secondary progressive MS, based on the revised McDonald criteria or were diagnosed with MS by an attending physician as noted in their medical recordsPatients with at least two medically confirmed clinical exacerbations within 24 months prior to consent or one exacerbation within 12 months prior to consentPatients with at least one lesion suspected to be MS on screening magnetic resonance imaging (MRI)Patients with 7 points or less in the Expanded Disability Status Scale during screeningPatients who were 20-65 years old at the time of consentPatients who can practice contraception until 90 days after final administration of the investigational drugPatients with no clinical or test findings suggesting acute recurrence based on evaluation by a neurologistExclusion criteriaDiagnosis of neuromyelitis optica and one of the three following three criteria: optic neuritis, acute myelitis, and satisfied at least two of the following three items: (1) spinal cord MRI lesion extending across at least three vertebral bodies, (2) no brain MRI lesions during onset (at least four cerebral white matter lesions or three lesions, one of which is around the lateral ventricle), and (3) neuromyelitis optica–immunoglobulin G (IgG) or antiaquaporin-4 antibody-positiveCurrently pregnant or nursingContraindication for MRI (eg, those with metal implants or a pacemaker) or cases in which MRI is difficult to perform (eg, claustrophobia)History of allergic or hypersensitive reaction to gadolinium contrastHistory of liver disease, including liver transplantation, viral hepatitis, autoimmune hepatitis, cirrhosis, and hepatic malignanciesLiver dysfunction determined by the screening test or baseline test (alanine aminotransferase, aspartate aminotransferase, γ-guanosine triphosphate, or alkaline phosphatase) exceeding twice the upper limit of normal and total bilirubin exceeding 1.5-fold the upper limit of normalHistory of malignant tumors in the past 5 years (however, patients deemed to have no recurrence for at least 5 years prior to consent can be enrolled)Varicella-zoster virus IgG antibody–negativePositive for syphilis serum reaction (treponema pallidum latex agglutination, rapid plasma reagin)positive for β-D glucan (exceeding the standard value) or T-spotpositive for antiaquaporin-4 antibodyhistory of human immunodeficiency virus infection or who have been confirmed positive by a screening testHistory of hepatitis B infection (hepatitis B surface antigen–positive or hepatitis B core antibody–positive), or patients who have been confirmed positive by a screening testHistory of stem cell transplantation, organ transplantation, and treatment for rejectionPhysical, mental, or social condition affecting the ability to provide consent to or complete the trialParticipation in other clinical trials that received the investigational drug within 4 months prior to enrollmentBlood donation (200 mL within 2 months, 400 mL within 3 months) prior to enrollmentPeripheral blood lymphocyte count <600/mm^3^ by screening or baseline examinationWith or suspected of having an infectious diseaseImmunocompromised patientsInflammatory bowel diseaseUse of the following prohibited concomitant therapies:interferon-β preparation (prohibited 1 month before trial enrollment); fingolimod hydrochloride (prohibited 6 months before trial enrollment); natalizumab (prohibited 3 months before trial enrollment); glatiramer acetate (prohibited 1 month before trial enrollment); dimethyl fumarate (prohibited 3 months before trial enrollment); drugs other than azathioprine that have immunosuppressive, immunostimulatory, or myelosuppressive effects (prohibited 3 months before trial enrollment); pulse therapy using corticosteroids (prohibited 1 month before clinical trial registration, except when MS recurs); plasmapheresis, immunoadsorption therapy, lymphocyte depletion therapy (prohibited from the time of consent acquisition); immunoglobulin preparation (prohibited 2 months before trial enrollment); vaccines (prohibited 1 month before trial enrollment, except when permitted by the investigator); other investigational drugs (prohibited 4 months before trial enrollment); nonsteroidal anti-inflammatory drug (liver damage at the time of screening should be checked, and for patients who take it regularly, this drug can be used in combination by fixing the dosage and administration. Additionally, when used for adverse events, it should be possible to use this drug within the minimum necessary range)Additional exclusion criteria:Patients with evident prolongation of the QT/QTc interval prior to the trial (eg, patients with repeating QTc interval>450 ms)Patients with a history of other risk factors for torsades de pointes (eg, family history of heart failure, hypokalemia, and long QT syndrome)History of severe drug or food allergyPatients with drug or alcohol dependence in the past or presentAsthma (excluding patients with no history of treatment or attack for at least 10 years)Diagnosis of epilepsy or patients with a history of seizures (excluding febrile seizures)Other pathological symptoms, illnesses, or history that may affect this trialOther factors resulting in unsuitability for this trial as deemed by the principal investigator; if such exclusion occurs, the specific rationale will be described in the trial results

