### Patient Clinicodemographic Characteristics

The following clinicodemographic information was recorded for each participant: (1) subject background (eg, birth date, sex, body height, body weight); (2) urine pregnancy test; (3) infectious disease or antibody test; (4) vital signs (blood pressure, pulse rate, body temperature, and breathing rate); (5) neurological symptoms rating scale (Expanded Disability Status Scale [EDSS] or functional disability scale); (6) clinical tests (hematological test, hematobiochemical test, or urine test); (7) 12-lead electrocardiogram; (8) echocardiography; (9) chest or abdominal X-ray; (10) abdominal computed tomography; (11) MRI; (12) peripheral blood gene expression level (reverse transcription–polymerase chain reaction); (13) frequencies of NK, NKT, T cells, or other lymphocyte subsets; (14) frequencies of Th1, Th2, or Th17 cells; (15) intestinal and oral microbiome; (16) adverse events; (17) combination drugs and important nondrug therapies; and (18) Columbia Suicide Severity Rating Scale.

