### Discontinuation Criteria

Discontinuation of involvement in the clinical trial may occur for any patient because of voluntary withdrawal or for any of the following reasons: (1) serious adverse events; (2) pregnancy; (3) alanine aminotransferase and aspartate aminotransferase >5-fold higher than the standard value upper limit; (4) total bilirubin exceeding 2.0 mg/dL; (5) number of peripheral blood lymphocytes <500/mm^3^ and administration of the investigational drug is stopped three times in a row without recovery, even after three tests; (6) occurrence of a grade-3 event based on Common Terminology Criteria for Adverse Events v4.0-JCOG; (7) new neurological symptoms with unpredictable MRI findings observed from the course of MS; (8) more than one recurrence of MS; (9) at least three courses of pulse steroid therapy performed; (10) an important management problem is discovered (subject noncompliance); (11) significant deviation from the protocol; (12) administration of the investigational drug is stopped at least three times, regardless of the reason; and (13) at the discretion of the principal investigator. If discontinuation occurs because of this final criterion, justification will be provided in the results report.

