### Statistical Methods

Patient clinicopathological data will be summarized using descriptive statistics for each group. The proportion of subjects with new or enlarged existing lesions on T2-weighted MRIs in each group will be calculated and compared using the Fisher exact test with 95% CIs. The proportion of data between groups related to the primary endpoint will also be compared using the Fisher exact test with 95% CIs. For time-to-event data such as relapse-free periods, Kaplan-Meier estimates will be calculated for each group and groups will be compared using the log-rank test. The expression rates of safety-related outcomes and adverse events will be calculated for each group. For various test values, a list of measured values will be created for each group. The summary statistics for each group and measurement time point will also be calculated.

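### As printed, the liver exclusion needs a raised enzyme and a raised bilirubin together, so two narrow patient profiles pass the numeric entry rules while already meeting a stopping criterion

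*Protocol article*

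**What the plan says.** **Entry.** The liver-dysfunction item in Textbox 1 (protocol article, Selection Criteria) rests on the screening or baseline test. It names ALT, AST, γ-GTP (printed under a slightly different name) and ALP, joined by *or*. It then sets the condition as "exceeding twice the upper limit of normal and total bilirubin exceeding 1.5-fold" the upper limit of normal. No other exclusion gives a number for a liver test. The rest are non-numeric: a history of liver disease, hepatitis B status, a note under the NSAID item that "liver damage at the time of screening should be checked", a clause on other illnesses that may affect the trial, and the principal investigator's judgement of unsuitability.

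**Stopping.** The Discontinuation Criteria list two separate liver reasons. Criterion 3 is "alanine aminotransferase and aspartate aminotransferase >5-fold higher than the standard value upper limit". Criterion 4 is "total bilirubin exceeding 2.0 mg/dL". The lead-in is permissive: "Discontinuation of involvement in the clinical trial may occur for any patient because of voluntary withdrawal or for any of the following reasons".

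**Data.** Each participant has "clinical tests (hematological test, hematobiochemical test, or urine test") recorded. Under Statistical Methods, "For various test values, a list of measured values will be created for each group", with summaries by time point.

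**The concern.** An entry limit for a safety laboratory value should be at least as strict as the limit at which the same value becomes a reason to stop. Otherwise a patient can be randomised and dosed with a result that the protocol itself gives as grounds for discontinuation. The printed *and* allows this: a very high value on one side passes as long as the other side is within its limit.

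The stake is avoidable dosing of such a patient, and reuse of the printed rule in a later trial. The primary outcome, its Fisher exact test and the stated power do not depend on this rule.

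**Working it through.** The plan gives no figure to reproduce here, so the check is to apply the printed rule and the likely intended rule to test patients.

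**Inputs**
- Entry, from Selection Criteria: E = any of the four enzymes > 2 × ULN; B = total bilirubin > 1.5 × ULN.
- Stopping, from Discontinuation Criteria: criterion 3 = ALT and AST > 5 × ULN; criterion 4 = bilirubin > 2.0 mg/dL.
- The article gives no bilirubin ULN. I assume a range of 1.0 to 1.5 mg/dL, so the entry limit 1.5 × ULN runs from 1.5 to 2.25 mg/dL.

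**Step 1: how many combinations each rule excludes.** E and B can each be yes or no, which gives 4 combinations. *E and B* excludes 1 of 4. *E or B* excludes 3 of 4.

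**Step 2: test patients.** A normal bilirubin is taken as 0.8 mg/dL and normal enzymes as 1 × ULN.

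| Patient | Printed *and* | *or* | Stopping criterion already met |
|---|---|---|---|
| ALT and AST both 6 ×, bilirubin normal | enters | excluded | 3 (6 > 5) |
| Bilirubin 2.5 mg/dL, enzymes normal | enters | excluded at every assumed ULN (2.5 > 2.25) | 4 (2.5 > 2.0) |
| ALT alone 6 ×, bilirubin normal | enters | excluded | none on the literal text; 3 only if its *and* means either |
| ALT alone 3 ×, bilirubin normal | enters | excluded | none |
| ALT 2.5 × and bilirubin 2.5 mg/dL | excluded | excluded | 4 |

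Only the first two rows show the conflict without a further assumption. The first meets criterion 3 whether its own *and* is read as both or as either.

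**Step 3: does a plain *or* close the gap?** For criterion 3 it does: anyone with ALT or AST above 2 × ULN is excluded, and 2 < 5. For criterion 4 it does only if 1.5 × ULN ≤ 2.0, that is, ULN ≤ 2.0 / 1.5 = 1.33 mg/dL. Take bilirubin 2.1 mg/dL with normal enzymes:
- ULN 1.0, 1.2 or 1.33: limits 1.5, 1.8 and 1.995, so the patient is excluded.
- ULN 1.4: limit 2.1, which 2.1 does not exceed, so the patient enters.
- ULN 1.5: limit 2.25, so the patient enters and meets criterion 4.

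**The case against.** The best counter-argument is that the article does not use *and* and *or* as strict logic. In the same list, the transplantation item joins stem cell transplant, organ transplant and rejection treatment with *and*, although any one is plainly meant. The liver item can be read the same way, as two thresholds either of which counts. That supports *or* as the intended meaning. It does not make the printed rule safe to follow, because the enzymes inside the same item are joined by *or*, and the change of connector invites the literal reading.

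A second argument is that the general clauses would stop a patient with both transaminases at 6 × ULN. Many such patients would probably be caught. But a numeric limit is there so that exclusion does not depend on judgement at each centre.

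Three stronger readings are tempting and should not be drawn:
- *Any isolated liver abnormality that passes entry already meets a stopping rule.* It does not. ALT at 3 × ULN meets none, and ALT alone at 6 × ULN meets none on the literal text.
- *The lymphocyte limits show that entry was designed to be stricter than stopping.* Entry is refused below 600/mm³, but the stopping rule is more than a threshold: "number of peripheral blood lymphocytes <500/mm^3^ and administration of the investigational drug is stopped three times in a row" without recovery. The two are not comparable enough to establish intent.
- *Patients with such values were enrolled, or would have had to be withdrawn.* The article shows no such patient, and its stopping list says that discontinuation may occur.

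**Conclusion.** The point holds in a narrow form and is minor. Followed to the letter, the liver exclusion leaves each part without a numeric limit while the other is within its own. It thereby admits two profiles that already meet criterion 3 or criterion 4. The result for criterion 3 needs no assumption. The test value of 2.5 mg/dL for criterion 4 gives the same result across assumed ULNs of 1.0 to 1.5 mg/dL. The documents give no frequency, so the number of patients affected cannot be sized and may be zero.

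This looks like a wording error, not a deliberate design choice, and the article alone cannot show which rule the sites applied. The effect is further limited because baseline values are collected and a monitoring committee audits safety data, so a pre-existing abnormality can be recognised afterwards.

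**What to change.** 1. Restate the exclusion as: any of ALT, AST, γ-GTP or ALP above 2 × ULN, *or* total bilirubin above 1.5 × ULN.
2. Confirm which rule the sites applied. If the full protocol already has *or*, correct the article only.
3. Check the screening and baseline liver values of the 30 analysed patients against criteria 3 and 4, and report any patient who already met one.

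An added entry cap of 2.0 mg/dL for bilirubin is optional. It matters only where the local ULN exceeds about 1.33 mg/dL.

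The cost is one connector and a review of values already collected. Enrolment closed in June 2021, so no dosing decision in this trial changes; the gain is a correct published rule and a confirmed baseline. The downside falls on any later trial that reuses the rule: a few extra screen failures, such as benign isolated hyperbilirubinaemia. The article gives no figure from which to estimate how many.
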